### 2.3. Sample Size

In this trial, the ratio of the pharmacopuncture group to the acupuncture group will be 2:1 in order to obtain data on the side effects (safety) of the pharmacopuncture while securing statistical power [38,39]. The sample size of this study was determined based on the study by Xian et al. [40]. The mean differences in PSQI scores before and after treatment in the experimental and control groups were estimated to be 6.9 (standard deviation = 2.51) and 4.93 (standard deviation = 2.70), respectively. Based on this, the effect size calculated using G Power software, version 3.1.9.4 (Franz Faul, Christian-Albrechts-Universittt Kiel, Kiel, Germany) was 0.92. The number of participants required is then 74 for the experimental group and 37 for the control group, given a 2:1 allocation ratio, two-sided significance level of 0.05, and 95% statistical power. Considering a dropout rate of 20%, the total sample size of the experimental and control groups will be 92 and 46, respectively.

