### 2.9. Outcome Measures

#### 2.9.1. Primary Outcome

The primary outcome measure will be the mean difference in the total Pittsburgh Sleep Quality Index (PSQI) scores pre- and post-intervention (between visits 1 and 11) between the two groups. The PSQI is the most commonly used self-report questionnaire to assess sleep quality and disturbances over the past month. It comprises 19 self-rated items and evaluates seven components: subjective sleep quality, sleep latency, sleep duration, habitual sleep efficiency, sleep disturbances, use of sleep medication, and daytime dysfunction. The total PSQI score ranges from 0 to 21, with higher scores indicating poorer sleep quality [44]. The PSQI score will be assessed at baseline, visit 6, post-intervention, and follow-up visits.

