#### 2.9.2. Secondary Outcomes

The secondary outcomes will be changes in the ISI, PSQI, and visual analog scale (VAS) scores of subjective symptoms accompanying insomnia, and the difference in quantity and quality of sleep recorded using a sleep diary and actigraphy during the trial period. The ISI and VAS scores of subjective symptoms accompanying insomnia, sleep diaries, and actigraphy will be checked at the baseline, visit 6, post-intervention, and follow-up visits. In addition, changes in scores on the Core Seven-Emotions Inventory Short Form (CSEI-S), Pattern Identification Tool-Insomnia (PIT-Insomnia), and body composition test between the pre- and post-treatment periods will be analyzed. The ISI is a self-report questionnaire designed to assess a patient’s subjective perception of insomnia severity. It consists of seven items rated on a 5-point Likert scale. The total ISI score ranges from 0 to 28 [45], with a higher score indicating more severe insomnia; the cutoff point for clinically significant insomnia is 15 [46].

We will assess the improvement in physical symptoms accompanying insomnia, such as headache, dyspepsia, and fatigue, using the VAS scale.

The PIT-insomnia, developed by Lee et al. [47] is a self-report questionnaire for assessing the pattern identification of insomnia.

The CSEI-S is a self-rating questionnaire used to assess the quantity of seven basic human emotions: joy, anger, thought, depression, sorrow, fear, and fright, based on the seven emotions theory in Korean medicine [48].

A sleep diary is a useful tool for obtaining sleep-related information and monitoring the treatment progress [49]. Eligible participants will be asked to complete a sleep diary after waking up daily. The sleep diary items included bedtime, waking time, sleep onset latency, sleep duration, number of awakenings, use of medications, and sleep satisfaction scores ranging from 0 to 100, with higher scores indicating greater sleep satisfaction.

The eligible participants will be asked to place an actigraphy device (ActiGraph wGT3X-BT; MTI Health Services Company, Pensacola, FL, USA) on their non-dominant wrists to obtain objective sleep-related information. Records from the actigraphy device at baseline, visit 6, post-intervention, and follow-up visits will be downloaded and saved. The extracted sleep-related variables will be used to compare the changes between the groups and their consistency with sleep diary records.

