### 2.13. Statistical Analysis

Continuous variables will be presented as means and standard deviations, while categorical variables will be presented as frequencies (%) and percentiles. The homogeneity of the demographic characteristics and baseline variables between the two groups will be evaluated to choose the appropriate analysis methods. The independent t-test or Mann–Whitney U-test will be used for analysis, depending on the normality of data distribution. If there were significant between-group differences in baseline variables or demographic characteristics, regression analysis with covariates (analysis of covariance) will be conducted. The primary and secondary outcome measures will be analyzed in the same manner. We will also examine the consistency between objective and subjective sleep-related data obtained from actigraphy and patient-reported questionnaires.

Additionally, we will analyze the changes in sleep parameters assessed using polysomnography and sleep-related hormones before and after treatment in participants who underwent polysomnography. Both the full analysis set (FAS) and per-protocol analyses will be conducted. The FAS is the primary analysis of effectiveness and safety. It will include all participants initially assigned to each group, except those who did not meet the eligibility criteria, those who had not received any intervention, or those who had not completed any outcome measurements. The per-protocol analysis will include participants who have completed more than seven sessions. All statistical analyses will be performed by an independent statistical expert blinded to the allocation and procedure using SPSS version 25 (IBM, Chicago, IL, USA). Statistical significance is set at *p* < 0.05.

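### The primary FAS removes randomised participants after an open allocation, and the named V1–V11 tests cannot use FAS members without V11 or draw on their V6 PSQI unless an imputation rule not shown applies

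*Protocol article*

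**What the plan says.** Section 2.13 (Statistical Analysis) is explicit about the set: "The FAS is the primary analysis of effectiveness and safety". It comprises everyone assigned, "except those who did not meet the eligibility criteria, those who had not received any intervention", and also without "those who had not completed any outcome measurements".

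Section 2.9.1 defines the primary outcome as the difference in total PSQI "scores pre- and post-intervention (between visits 1 and 11) between the two groups". It also fixes the measurement times: "The PSQI score will be assessed at baseline, visit 6, post-intervention, and follow-up visits". Table 1 agrees (V1, V6, V11, V12).

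For the test, Section 2.13 says "The independent t-test or Mann–Whitney U-test will be used for analysis", chosen on normality, with ANCOVA if baseline variables differ significantly between groups. Secondary outcomes are analysed in the same way. PSQI is also listed there (Section 2.9.2): "The secondary outcomes will be changes in the ISI, PSQI, and visual analog scale (VAS) scores".

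Three other places bear on this:

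- **Section 2.3** raises 74/37 to 92/46: "Considering a dropout rate of 20" per cent.
- **Section 2.6** says participants and practitioners cannot be blinded, and the investigator opens the allocation envelope.
- **Section 2.12** ends participation, as well as treatment, for several post-randomisation events. These include a change in sleeping pills and attendance at fewer than seven sessions.

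The article states no rule for a missing V11 score.

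**The concern.** There are two linked problems.

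**The set.** All three exclusions take effect after randomisation, when the arm is known. Declining the first session can depend on which arm was drawn. Nothing limits the ineligibility exclusion to facts that existed before randomisation, or requires it to be judged without sight of the arm.

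**The test.** The FAS keeps a participant who has any outcome measurement, for example V6 but not V11. Each named test compares one value per person, the V1–V11 change or V11 adjusted for baseline. Without imputation, such a participant belongs to the set but contributes nothing to the result. The V6 PSQI, which could carry information about why V11 is missing, does not enter the primary test.

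Some events that end participation under Section 2.12 may follow a poor response. If poor early responders leave one arm more often than the other, a comparison of those with V11 is biased, and the direction depends on which arm loses more.

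**Working it through.** **1. The plan's own figures.** With means 6.9 (SD 2.51) and 4.93 (SD 2.70), the difference is 1.97. The pooled SD is √[(2.51² + 2.70²)/2] = 2.607, so d = 1.97/2.607 = 0.756. A two-sided Mann–Whitney calculation at 5% and 95% power, 2:1, with relative efficiency 0.955, gives 37 control and 74 experimental, as stated. (The printed effect size of 0.92 does not follow from these inputs; that is a separate matter.) Enrolled numbers are 74/0.8 = 92.5 and 37/0.8 = 46.25, against the stated 92 and 46.

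**2. Power is not the issue.** At 20% loss, 0.2 × 138 ≈ 28 participants lack V11, leaving about 74/37. The t-test then has about 96% power at d = 0.756, against 98.6% with no loss and 93.4% at 30% loss.

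**3. Size of the bias.** The documents give no correlations and no dropout by arm. The assumptions are:

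- PSQI correlations: baseline–V6 0.5, baseline–V11 0.45, V6–V11 0.7, with equal SDs at the three visits.
- SD of the V1–V11 change: 2.6. True difference: 1.97.
- Within each arm, the participants with the smallest V6 improvement are the ones lost.

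The correlation between V6 change and V11 change is (1 − 0.5 − 0.45 + 0.7)/√[2(1 − 0.5) × 2(1 − 0.45)] = 0.75/√1.1 = 0.715.

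If a fraction p of an arm is lost this way, the mean change of those remaining rises by SD × 0.715 × φ(z)/(1 − p), where z is the normal quantile at p and φ the normal density.

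- p = 0.15: φ/(1 − p) = 0.233/0.85 = 0.274
- p = 0.30: φ/(1 − p) = 0.348/0.70 = 0.497

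The shift in the treatment difference is 2.6 × 0.715 × (0.274 − 0.497) ≈ −0.41 for 15%/30% (experimental/control), and +0.41 for 30%/15%. If loss is only partly driven by V6 change (correlation 0.5), the shift halves to about 0.21. At 0.3 it is about 0.12.

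Simulation of 92/46 agrees:

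| Loss, experimental/control | Change-score test, loss fully V6-driven | Change-score test, partly (0.5) | Analysis using V6 |
|---|---|---|---|
| 15%/30% | 1.56 | 1.75 | about 1.97 |
| 30%/15% | 2.39 | 2.18 | about 1.97 |
| 20%/20% | no bias | no bias | no bias |

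The analysis using V6 predicts missing V11 from baseline and V6 within arm and then adjusts for baseline, as an analogue of a likelihood model.

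A milder mechanism, with logistic dependence on V6 change, about 19%/25% loss and V6–V11 change correlations of 0.3 to 0.7, gives 1.83 to 1.91 for completers and 1.96 to 1.97 when V6 is used.

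**4. Precision at balanced 20% loss.** The change-score SE is about 0.51 and the model's about 0.43. Complete-case ANCOVA already gives 0.44. The arithmetic shows why: baseline adjustment multiplies the SE by √[(1 − 0.45²)/(2(1 − 0.45))] = √(0.7975/1.1) = 0.85, and 0.51 × 0.85 ≈ 0.43. The gain is almost wholly from baseline adjustment, not from V6.

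**The case against.** The strongest reply is that the article is a condensed protocol and imputation rules usually sit in the full protocol or the SAP. A reader might infer that the primary result is a complete-case analysis that treats the 20% loss as completely random. The article does not say so. It keeps a participant with V6 but no V11 in the FAS and leaves open how that person enters the test. This stands, and the point is worded accordingly.

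A reader might also infer that the V6 PSQI is thrown away. It is not: PSQI change is also a secondary outcome. V6 is only absent from the primary test.

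A third tempting reading joins the FAS eligibility exclusion to the withdrawal criterion for a medical condition diagnosed during the trial. They are different rules. The FAS wording is most naturally read as entry eligibility, although it does not say when or by whom that is judged.

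Other fair points:

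- Allocation and the first session both fall at V1, so the window for refusing treatment is short. The effect of the FAS exclusions has not been quantified.
- The unequal dropout splits are assumptions. The only rate given is 20% overall, and equal 20% loss produces no bias.
- PSQI covers the past month, so the V6 score partly reflects time before treatment. V6 may predict V11 less well than assumed.
- A repeated-measures model cannot use participants with no post-baseline PSQI, so it does not by itself achieve an analysis of everyone randomised.

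These limit the size of the point and shape the fix. They do not remove the stated exclusions, or the mismatch between a set that admits people without V11 and tests that cannot use them.

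**Conclusion.** The point holds in limited form. The article itself states the post-allocation exclusions and the single-time-point tests, so this is a weak choice of method and not merely omitted detail. Whether FAS members without V11 are actually dropped is unresolved, because a rule may exist in a document not shown.

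The risk is bias under differential, response-related loss. On the assumptions given, a true difference of 1.97 becomes about 1.56 to 1.75, or about 2.2 to 2.4, depending on which arm loses more. Milder mechanisms shift it by about 0.06 to 0.14 points. Power and precision are not grounds for the change: power stays near 96% at the planned loss, and baseline adjustment alone delivers nearly all the SE gain. The change should be made, since it is cheap and uses data already scheduled.

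**What to change.** 1. Analyse participants in their assigned arm, whether or not they received treatment.
2. Make the primary analysis a mixed model for repeated measures on V6, V11 and V12 PSQI, with treatment, visit, treatment-by-visit, baseline PSQI and institution. The V11 treatment contrast is primary.
3. Exclude for ineligibility only on facts that existed before randomisation, judged by someone blind to arm.
4. Add a delta-adjusted sensitivity analysis for missing V11. It should also cover randomised participants with no post-baseline PSQI, whom the model cannot use.

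The cost is revised analysis wording and modest programming, which the MIXED procedure in the planned SPSS package can handle. No new visit or measurement is needed. The downside is reliance on a missing-at-random assumption, which item 4 is there to test.

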#### 2.7.2. Control Group: Acupuncture

The comparator treatment will be acupuncture, which is the most commonly used method for treating insomnia in Korean medical practice according to a previous survey [31]. Similar to the pharmacopuncture treatment, the health practitioners will decide the acupuncture protocol in terms of the acupuncture type, acupoints, needle type, depth of insertion, and retention time, depending on the patient’s condition.

Nevertheless, based on previous studies on insomnia and consensus between Korean medicine specialists in neuropsychiatry [42,43], we primarily selected the acupoints GV20, EX-HN3, and bilateral HT7, PC6, BL63, and KI4, but we will allow the practitioners to modify the acupoints used according to their clinical decisions. All treatment-related parameters will be recorded for analysis.

Both pharmacopuncture and acupuncture will be performed by Korean medicine doctors with more than 2 years of experience in acupuncture practice. All practitioners will have completed the standard operating procedure training related to pharmachopuncture and acupuncture administration before this trial’s initiation. To improve adherence to the intervention, treatment, and assessment will be performed through reservation, and participants will be notified of the date of their visit in advance via phone. In addition, investigators will check the participants’ concomitant drug changes and adverse events (AEs) at every visit.

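### The blinded statistician promised in section 2.13 cannot stay blinded under 2:1 allocation, so the blind does not protect the data-dependent choice of test and covariates

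*Protocol article*

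**What the plan says.** Section 2.13 of the protocol article gives all analyses to one person: "All statistical analyses will be performed by an independent statistical expert blinded to the allocation and procedure". The same section leaves three things to the data:

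- The groups are compared on demographic and baseline variables, and the result guides the choice of method.
- The test is an independent t-test or a Mann–Whitney test, according to normality.
- Analysis of covariance is used only if a baseline or demographic difference is significant. No covariates are named.

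The primary and secondary outcomes follow the same scheme.

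Section 2.3 sets the allocation: "the ratio of the pharmacopuncture group to the acupuncture group will be 2:1". After allowance for dropout, "the total sample size of the experimental and control groups will be 92 and 46, respectively". Section 2.6 uses block randomisation stratified by institution, which keeps the split near 2:1 at each site. Section 2.7.2 adds: "All treatment-related parameters will be recorded for analysis". Section 2.9.4 makes pharmacopuncture expense one of the cost variables.

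**The concern.** Coded labels can mask an analyst only if the codes are the sole route to the arms. Here one group is planned at twice the size of the other, and the sizes are published. An analyst who sees any count by group knows which code is pharmacopuncture.

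The order of events in section 2.13 makes this matter. The baseline comparison needs data split by group, and it comes before the decision on method and covariates. Those decisions would therefore be made by someone who can tell the arms apart.

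The trial has few other protections at this point. Section 2.6 says that participants and practitioners cannot be blinded, and section 2.9.1 makes a self-reported questionnaire, the PSQI, the primary outcome. Blinded assessors add little when an unblinded participant supplies the answers. A report that claimed a blinded analysis would claim something the design does not deliver.

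**Working it through.** **Inputs.** From section 2.3: 2:1 allocation; 74 and 37 evaluable; 92 and 46 randomised; 20% dropout; "two-sided significance level of 0.05, and 95% statistical power". From section 2.6: blocks within institution.

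**Step 1: reproduce the planned sizes.** Dividing by (1 − 0.20) gives 74/0.8 = 92.5 and 37/0.8 = 46.25. The plan states 92 and 46, which agrees apart from rounding down.

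The evaluable sizes also follow from the stated changes and standard deviations:

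- d = (6.9 − 4.93)/√((2.51² + 2.70²)/2) = 1.97/2.607 = 0.756.
- At 2:1, two-sided 0.05 and 95% power, a Mann–Whitney test (relative efficiency 3/π) needs 74 and 37, with power 0.953.

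The printed effect size of 0.92 does not follow from these inputs. That is a separate matter and changes nothing here, because either value leaves the arms at 2:1.

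**Step 2: worst case for the planned total dropout.** 20% of 138 is 27.6, about 28. If all 28 came from pharmacopuncture, 92 − 28 = 64 would remain against 46, and the larger group would still be pharmacopuncture.

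**Step 3: when size stops identifying the arm.** Let p and c be the proportions lost from pharmacopuncture and acupuncture. The sizes are equal when 92(1 − p) = 46(1 − c), so p = (1 + c)/2. With c = 0, p = 50% (46 against 46). With c = 20%, p = 60% (36.8 against 36.8).

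**Step 4: chance that size points to the wrong arm or to neither.** Take the retained numbers as independent binomials, E ~ Bin(92, 1 − p) and C ~ Bin(46, 1 − c), and compute P(E ≤ C). Only the first row uses the plan's dropout rate; the other rates are assumptions that show the range.

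| Loss, pharmacopuncture / acupuncture | Expected sizes | P(E ≤ C) |
|---|---|---|
| 20% / 20% | 73.6 / 36.8 | 6e-14 |
| 30% / 10% | 64.4 / 41.4 | 3e-6 |
| 40% / 10% | 55.2 / 41.4 | 0.005 |
| 40% / 0% | 55.2 / 46 | 0.03 |
| 45% / 5% | 50.6 / 43.7 | 0.10 |
| 50% / 0% | 46 / 46 | 0.54 |

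**Step 5: set the steps of section 2.13 in order.** The groups are compared at baseline, which needs a split by group. The split shows the sizes, and the sizes show the arms. The method and covariates are then settled. The blind ends at the first of these steps, before the last.

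**The case against.** The strongest reply is that most of the harm comes from a different weakness. Choosing the test by normality and the covariates by significance depends on the data whoever does it. Under 1:1 allocation with A/B codes the analyst could still see which method gave the smaller p-value; knowing the arms adds only the direction. This is right, and it is why the fix starts with a fixed primary model.

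A second reply is that normality can be judged on pooled data and that the baseline comparison needs no outcome data. The result need not be visible when the model is chosen. That also stands. Section 2.13 does not say that outcomes would be seen first, but it sets no barrier either, and the baseline comparison itself cannot be done unsplit.

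A third reply is that coding of labels, timing of the merge and sign-off belong in an analysis plan that is not shown. Their absence is indeed no fault. The point rests on something stated: a blind covering all analyses. An unseen plan could fix the choices in advance, but it could not make groups of 92 and 46 look alike to an analyst using the real group variable.

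Treatment parameters and costs are secondary clues. The primary PSQI comparison does not need them, and they could be released later.

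A reader might also infer that the statistician judges, with the arms known, who enters the full analysis set and the per-protocol set. The text does not support this. Section 2.13 gives those decisions to nobody in particular, its full-analysis-set exclusions are largely factual, and per-protocol status is a count of sessions.

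**Conclusion.** The point holds in limited form. The blinding in section 2.13 cannot be kept for any analysis split by group, and the section requires such a split before the test and covariates are settled. At the planned dropout rate, identification of the pharmacopuncture arm is practically certain. It becomes doubtful only with very unequal losses, near 50% against none.

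This rests on two assumptions: that the analyst works with the real group variable under neutral codes, and that losses are roughly binomial within each arm. If the group variable were withheld until the method was fixed, the problem would not arise, but the present order of steps rules that out.

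It would be going too far to conclude that the analysis will be biased. The calculation measures whether the arms can be inferred, not any shift in the estimate, and the triggers for the test and for covariance analysis are partly rule-based. The change is worth making because it is cheap and the trial is open-label with a self-reported primary outcome.

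**What to change.** Revise section 2.13 as follows.

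1. Replace the data-dependent choice with one primary model whose covariates are named in advance, for example analysis of covariance of post-treatment PSQI on baseline PSQI and site. With baseline in the model, the group effect is the same as for change from baseline, so the primary outcome in section 2.9.1 is kept.
2. Finalise the full-analysis-set and per-protocol lists, and lock the SPSS syntax, on a dataset without the real group variable (or with permuted labels) and without treatment-parameter or cost data.
3. Merge the real allocation only after the lists and syntax are signed off.
4. Describe the analysis as pre-specified and locked before unblinding, and drop the word blinded.

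Step 1 is needed for step 2 to work. Permuted labels cannot show a real baseline imbalance, so locked syntax could not carry the present conditional rule.

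The cost is a small amount of extra programming and the loss of the data-driven choice of method. Sample size, sites and participants are unaffected.
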